### Immunology substudy

Integrated profiles of innate immune cell function will be generated for each child using principal components analysis followed by hierarchical clustering.^65 66^ This data -reduction method identifies whether absolute levels of specific markers or relative differences between markers differentiate children into groups. The resulting innate immune profiles will be compared between HIV-SAM, HIV-negative children with SAM and well-nourished groups using univariable tests and multivariable analysis of variance of the principal components.

To address the relationship between immune function and infections, regression analyses will determine whether baseline innate immune profiles (or the individual parameters defining them) are associated with the infectious morbidity or mortality during hospitalisation, using logistic models for binary outcomes and linear models for duration. Key clinical characteristics, including age, sex, oedema and baseline WHZ, will be added to models to investigate their confounding effects. Multivariable stacked regression methods will be used to compare the impact of different factors on severe bacterial infections based on heterogeneity tests.

To determine whether treatment for SAM restores innate immune cell antibacterial function, mixed effects regression models will compare longitudinal changes in individual immune parameters, and the principal components calculated from the weights identified at baseline (which include well-nourished controls). Similarities and differences in longitudinal immune profiles will be compared between groups using non-metric multidimensional scaling.^65 67 68^ This approach will group children according to their composite innate immune function, allowing the duration and variability of immune restoration to be evaluated over the course of nutritional rehabilitation. Binary logistic regression will determine whether innate immune profiles at discharge are associated with morbidity or mortality during follow-up.

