## Introduction

Malnutrition underlies almost half of all childhood deaths in developing countries.^1^ Severe acute malnutrition (SAM) is defined by a weight-for-height Z-score (WHZ) <–3, mid-upper arm circumference (MUAC) <115 mm and/or bilateral pitting oedema.^2^ Current treatment guidelines distinguish two groups: (i) children with uncomplicated SAM who can be managed in the community and (ii) children with complicated SAM, who are hospitalised and undergo resuscitation, stabilisation and nutritional rehabilitation. In-hospital mortality in children with complicated SAM remains high despite the implementation of WHO guidelines.^3^ Furthermore, SAM presents as two major clinical phenotypes: non-oedematous SAM (marasmus), characterised by severe wasting, and oedematous SAM (kwashiorkor), a more complex syndrome characterised by bilateral pitting oedema, steatosis and diarrhoea.^4 5^ Despite differing clinical outcomes, treatment protocols are the same for both oedematous and non-oedematous SAM.

A contributory factor to high inpatient mortality is the co-occurrence of HIV infection in around one-third of children hospitalised for SAM in sub-Saharan Africa.^6 7^ While new HIV infections in children have declined,^8^ a substantial number of infected children are diagnosed late and present with malnutrition. There is also a growing population of HIV-exposed uninfected (HEU) children who have immune abnormalities, poor growth and higher risk of mortality and infectious morbidity.^9^ Hence, HIV has transformed the epidemiology and outcomes of SAM.^10^ Even with standardised treatment approaches, inpatient deaths are almost fourfold higher among HIV-positive children with SAM (herein termed HIV-SAM) compared with HIV-negative children with SAM (30.4% vs 8.4%), for reasons that remain unclear^10^; this mortality is threefold higher than would be expected from anthropometric parameters alone.^10^ Management of HIV-SAM is particularly challenging because HIV fundamentally alters the clinical presentation of malnutrition and the response to treatment. Children with HIV-SAM are more stunted and wasted; have a higher frequency of persistent diarrhoea; tend to have delayed nutritional recovery and have a more complicated clinical course than HIV-negative children with SAM.^10^

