### Immunology substudy

Bacterial infections are common among children hospitalised for SAM^23 48–50^ and mortality is driven by a range of species,^48 50–53^ consistent with generalised defects in innate antibacterial defence. Increased infectious morbidity and mortality persist after discharge from hospital,^10 17 54^ suggesting that restoration of antibacterial immune responses may lag behind nutritional rehabilitation. A recent randomised trial in children with SAM confirmed that deaths following hospitalisation were predominantly due to bacterial infections but were not prevented by daily co-trimoxazole prophylaxis.^17^ Collectively, these observations highlight that children remain vulnerable to infection despite current treatment approaches; targeting persistent immune dysfunction could plausibly reduce infectious mortality after discharge.^24^

Multiple innate and adaptive immune mediators are dysregulated in malnutrition.^24 27 55^ However, few studies have assessed cellular immune function in malnourished children; most existing studies were undertaken decades ago on small cross-sectional cohorts without the benefit of recent advances in immunology techniques.^27^ Immune dysfunction in SAM likely reflects both *intrinsic* defects, whereby immune cells lack capacity to adequately respond to infection, and *extrinsic* defects, where cells have intact antibacterial capacity but are chronically modulated by the systemic pro-inflammatory environment which characterises SAM (ie, heightened pro-inflammatory cytokines^44^ and circulating bacterial antigens^23 56 57^). Systemic inflammation is directly associated with mortality in SAM^23^ and driven by multiple comorbidities, including bacterial translocation from the damaged gut into the blood, subclinical infections and metabolic dysregulation.^44 58 59^ The implications of innate immune cell dysfunction for subsequent acquisition of infections and infectious mortality have not been investigated.

We hypothesise that (i) antibacterial functions of innate immune cells are compromised in SAM due to a combination of intrinsic and extrinsic defects; (ii) innate immune cell function is independently associated with infectious morbidity and mortality during hospitalisation for SAM; and (iii) nutritional rehabilitation only partly restores innate immune cell function, leading to an ongoing risk of bacterial infections post discharge.

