### Immunology substudy

Up to 200 children with SAM and 200 well-nourished controls will be included in a cross-sectional analysis of innate immune cell function during hospitalisation. Assuming similar infectious mortality to a recent Kenyan study (15%),^17^ a cohort of 200 provides 80% power to detect associations between immune profiles and infectious mortality at an OR of 1.7 and two-sided alpha of 0.05. We will aim for 100 children with longitudinal analysis of innate immune cell function at discharge, 12, 24 and 48 weeks post discharge.^17^

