### Observational cohort

The primary comparison will be the clinical and nutritional outcomes of children with HIV-SAM compared with HIV-negative children with SAM. We will review all deaths and adjudicate clinical diagnoses and causes of death to ensure robust and consistent data across sites. We will compare each participant’s clinical management to WHO guidelines to identify any contributory factors in hospital care. Factors associated with outcomes during hospitalisation (eg, mortality, nutritional recovery) will be determined for each group (HIV-SAM and HIV-negative children with SAM) using multivariable analysis (Cox models for time-to-event data, linear models for continuous outcomes). Factors associated with outcomes over 48 weeks post discharge (hospital readmission, morbidity and mortality, relapse, anthropometry, body composition and response to ART) will be determined for each group (HIV-SAM and HIV-negative children with SAM) using multivariable analysis (Cox models for time-to-event data, linear models for continuous outcomes). HIV-positive children with SAM and HIV-negative children with SAM will be included in one model together with the risk factors, and interaction tests will be used to investigate whether associations between risk factors and outcomes differ between the two groups of children. We will evaluate the ability of MUAC at discharge to predict long-term outcomes using receiver-operator-characteristic (ROC) analysis, in the whole cohort and within the subgroups of HIV-SAM and HIV-negative children with SAM. We will then evaluate whether addition of other variables improves the predictive capacity of MUAC (using WHO criteria in those >6 months, and published data for children <6 months^62^) for each group, including body composition, haemoglobin, albumin and CRP, plus CD4%, viral load and timing of ART initiation (HIV-SAM only). We will construct multivariable models and compare them with MUAC alone using the net-reclassification index.

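### The linear model for duration of in-hospital infectious morbidity makes no provision for death, which can end the episode and is hypothesised to depend on the same immune profiles

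*Protocol article*

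**What the plan says.** - **Model.** In the Protocol article, Analysis, Immunology substudy, regression is to show whether baseline innate immune profiles "are associated with the infectious morbidity or mortality during hospitalisation", "using logistic models for binary outcomes and linear models for duration". Duration is not defined; in this sentence it reads most naturally as duration of infectious illness. Nothing is said about a child who dies before the illness resolves.
- **Hypothesis.** Substudies, Immunology substudy, hypothesises that "innate immune cell function is independently associated with infectious morbidity and mortality during hospitalisation for SAM". The exposure in the duration model is therefore expected to be related to death.
- **Size.** Sample sizes, Immunology substudy, takes 200 children and 15% infectious mortality as giving "80% power to detect associations between immune profiles and infectious mortality at an OR of 1.7 and two-sided alpha of 0.05". It gives no figure for the duration outcome and does not say that the 15% is in-hospital mortality.
- **Background mortality.** The Introduction cites inpatient deaths of 30.4% in HIV-positive and 8.4% in HIV-negative children.
- **Comparable outcomes elsewhere.** Analysis, Observational cohort, uses "Cox models for time-to-event data, linear models for continuous outcomes" for in-hospital outcomes. Analysis, Enteropathy substudy, uses Kaplan-Meier, log-rank and Cox methods for time to nutritional recovery.
- **Data.** Under Daily procedures, the study clinician records every day until discharge whether acute infections have resolved.

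**The concern.** A linear model treats duration as a complete measurement on every child. For a child who dies with the infection unresolved, time to resolution is never observed, only the time to death. If death were unrelated to the immune profile, this would mainly shrink the effect. Here the substudy's own hypothesis links the two, so the truncation is informative: children with harmful profiles are more likely to have their episode cut short.

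At stake is the interpretation of the duration result. A profile that raises the risk of death is pulled towards shorter illness, so a real prolonging effect can be diluted or missed, and the duration and mortality results from the same analysis may disagree for reasons that are not biological.

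**Working it through.** **1. The plan's own figure.** There is none for duration. The only stated power is for mortality. For a continuous predictor, with the odds ratio taken per SD (the unit is not given), n = (1.96 + 0.84)² / [p(1-p)(ln OR)²]. With p = 0.15 and OR = 1.7, n is about 219 for 80% power, and power at n = 200 is 76.4%. The detectable OR at n = 200 is 1.74, close to 1.7, so the per-SD reading is reasonable and is used below. The gap in power is a separate matter.

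**2. Inputs.**
- From the article: n = 200; 15% mortality (0.15 × 200 = 30 children); OR 1.7; the inpatient range 8.4–30.4%.
- Assumed: OR per SD; time to resolution gamma with mean 8 days (shape 3); mean day of death 3, or later (up to 7); mortality 7.5% as a lower case, because the 15% may not be in-hospital. Deaths are kept at observed time, so recorded duration = min(time to resolution, time to death).

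**3. Approximate formula.** With no true effect on illness length, slope ≈ -p(1-p) × ln(OR) × L, where L is the mean number of days lost when a child dies. With a true effect β that shows mainly in survivors, slope ≈ (1-p)β - p(1-p) ln(OR) L.
- 15% mortality, death about day 3: L is at least 8 - 3 = 5. Slope ≈ -0.15 × 0.85 × 0.531 × 5 = -0.34 day/SD.
- Same case, true β = +0.8: 0.85 × 0.8 - 0.34 = +0.34.
- 30% mortality, β = +0.8: 0.70 × 0.8 - 0.30 × 0.70 × 0.531 × 5 = 0.56 - 0.56, about zero.
- The sign reverses only if β < p × ln(OR) × L: about 0.15 × 0.531 × 5 = 0.40 day/SD at 15%, and 0.30 × 0.531 × 5 = 0.80 day/SD at 30%.

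**4. Simulation of the same model at n = 200, deaths at observed time.**

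| Case | Slope, true 0 | Falsely shorter (nominal 2.5%) | Slope, true +0.8 |
|---|---|---|---|
| 15% mortality, mean death day 3 | -0.35 | 17% | +0.32 |
| Lower mortality (7.5%) or later deaths | -0.14 to -0.20 | 6–8% | up to +0.62 |
| 30% mortality | about -0.59 | 42% | about 0 |

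**5. A different data model.** Time to resolution is Weibull (shape 2) with median 10 days, death time is exponential, and the death hazard ratio is 1.7 per SD. The null slopes are -0.28, -0.52 and -0.92 day/SD at 8.4%, 15% and 30.4% mortality, with 10%, 24% and 68% falsely shorter results. At 15%, a true +0.5 becomes -0.10, +1.0 becomes +0.29 and +2.0 becomes +1.02. The direction is the same; the size differs.

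**6. Excluding deaths.** In the first model death does not depend on illness length once the profile is fixed, and a survivors-only slope is essentially unbiased (0 stays about 0; +0.8 stays about +0.8). In the second, longer illnesses carry more exposure to death, and the survivors-only slope is biased downward (at 15%, 0 becomes -0.25 and +1.0 becomes +0.68). Whether exclusion is safe therefore depends on an assumption the data cannot settle.

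**The case against.** **The scoring of deaths is not stated.** A reader might infer that a child who dies early is recorded with a short, favourable duration. The article does not say so. Deaths could be excluded or assigned a worst value, and such derivation rules commonly sit in an analysis plan that is not shown. This stands, and the missing rule is not itself the finding. The finding is that the named model has no natural place for death: the two obvious ways of running it are biased or depend on an untestable assumption.

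**Harmful profiles need not look protective.** A reader might infer that they will. The calculations do not support that as the general result. Dilution is usual, and reversal needs a small true effect or high mortality.

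**Mortality and timing may be milder than assumed.** The 15% is not stated to be in-hospital, and Substudies, Immunology substudy, cites the same source for deaths after hospitalisation. The 30.4% is a background figure for HIV-positive children only. Early deaths will often have no immune profile: children who die before enrolment are ineligible, baseline sampling waits for clinical stability (Table 2 footnote), severely anaemic children are not bled, and the substudy needs more than 2 mL of blood. With 7.5% mortality and mean death on day 5–7, the null slope is only -0.12 to -0.14 day/SD, with 5–6% falsely shorter results. This limits the size, not the direction.

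**Limited consequence.** Infectious mortality is modelled in the same sentence, so harm through death would be visible there, and the Analysis section calls all analyses exploratory. Both are true. Neither corrects the duration estimate, and p values that are to be read as strength of evidence are distorted all the same.

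**Conclusion.** The point holds as a poorly suited model choice of moderate importance, confined to one analysis in one substudy. The article fixes a linear model for an outcome that death can end, hypothesises that death is related to the exposure, and uses time-to-event methods for comparable in-hospital outcomes elsewhere.

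If deaths are kept at observed time, the bias is towards shorter illness: about -0.14 to -0.35 day/SD under a true null at 7.5–15% mortality, with 6–17% falsely shorter results at n = 200. These figures rest on OR 1.7 per SD, a mean illness of 8 days and assumed death times. Other plausible times move them in either direction, so they illustrate scale rather than predict it. The documents do not support saying that fatal cases are scored as mild, or that harmful profiles will generally appear protective.

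**What to change.** In Analysis, Immunology substudy, replace the linear model for duration with:

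- **Main analysis:** time to resolution of infection, with death as a competing event. Use a cause-specific Cox model, supported by cumulative incidence curves or a subdistribution model. This matches the time-to-event methods in the observational cohort and enteropathy sections.
- **Alternative:** a ranked outcome in which death ranks worst and survivors are ordered by duration.
- **Discharge with unresolved illness:** children generally leave when complications are resolving and they are clinically well, so censoring them may be informative. Add a sensitivity analysis that treats discharge as resolution or as a separate competing event.
- **Survivors-only duration:** report descriptively.

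Cost: no new data collection, since resolution is recorded daily and deaths are captured by daily physician review. There is slightly more analysis work, and results appear as hazard ratios rather than differences in days.

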## Study design

HOPE-SAM is a longitudinal observational cohort study, enrolling between 600–800 children aged 0–59 months admitted with complicated SAM to the tertiary paediatric wards at two sites in Zimbabwe (Parirenyatwa Hospital and Harare Children’s Hospital) and one in Zambia (University Teaching Hospital, Lusaka). Both HIV-positive and HIV-negative children will be enrolled. Throughout this paper, ‘SAM’ refers to all children, regardless of HIV status; where analyses specifically compare children by HIV status, groups are identified as HIV-positive children with SAM (HIV-SAM) and HIV-negative children with SAM. All participants with SAM are followed for 48 weeks post discharge, with longitudinal data collection and blood sampling. The study contains four nested substudies as shown in figure 1. A subgroup of children will be recruited to the enteropathy substudy for which they will have the same follow-up procedures but more intensive biological specimen collection including stool (all time points), urine after lactulose-mannitol (LM) challenge as an assessment of intestinal permeability and nasogastric aspirate (baseline only); these children are also included in microbiota and metabolomics substudies. Children with SAM for whom blood samples are available are included in the immunology substudy, for which circulating inflammatory mediators will be assayed; functional cellular immunology assays will be conducted for all children in the immunology substudy with sufficient sample volume (>2 mL) recruited after June 2017. A group of healthy children recruited from the same hospitals and communities, who are well-nourished and matched to children in the enteropathy substudy by age and HIV status, will have data and specimens collected to provide normative data for the laboratory substudies; these well-nourished controls will not be followed longitudinally.

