## Study procedures

Study procedures are outlined in table 2.

**Table 2 T2:** Summary of procedures in observational cohort

Assessment	Hospitalisation		Post discharge*				
	Baseline†	Discharge‡	2 weeks	4 weeks	12 weeks	24 weeks	48 weeks
Caregiver informed consent to join observational cohort	x						
Summary checklist	x						
Locator information§	x						
Acute admission information	x						
Baseline data	x						
Daily clinical review¶	Daily during hospitalisation						
Blood collection**	x	x			x	x	x
HIV testing††	x						
CD4 count and viral load (HIV-infected children only)	x				x	x	x
Full blood count‡‡	x	x			x	x	x
Anthropometry	x	x	x	x	x	x	x
Skinfold thickness§§		x	x	x	x	x	x
Body composition¶¶	x	x	x	x	x	x	x
Discharge data collection		x					
Daily morbidity diary			Daily during follow-up period by caregivers				
Follow-up clinic: history, examination, morbidity and mortality data			x	x	x	x	x

*Windows will be created around these post-discharge time-points to maximize follow-up for caregivers who miss visits or are unavailable, as follows: 2 weeks (optimal window from 1 week to 2 weeks + 6 days; allowable window up to 2 weeks + 6 days); 4 weeks (optimal window 3-5 weeks, allowable window up to 9 weeks + 6 days); 12 weeks (optimal window 10-14 weeks, allowable window up to 19 weeks + 6 days); 24 weeks (optimal window 20-28 weeks, allowable window up to 43 weeks + 6 days); 48 weeks (optimal window 44-52 weeks, allowable window up to 71 weeks + 6 days). †Children will be enrolled as soon as possible after hospitalisation and will undergo baseline investigations as soon as possible after enrolment. This is to provide a window of opportunity to time collection of research specimens with clinical specimens, and to ensure that the child is clinically stable before undertaking research investigations.

‡The discharge procedures will be undertaken on the day of discharge or as close as possible to that date.

§Locator information will be updated at subsequent visits if caregivers have moved or changed contact details.

¶A clinical review will be undertaken every day between admission and discharge by the study clinician.

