## Study outcomes and risk factors

The main study outcomes are clinical (mortality, morbidity and relapse of malnutrition) and nutritional (weight, height, MUAC, leg length, head circumference, mid-thigh circumference, skin-fold thickness and body composition by bioimpedance vector analysis) assessed over 48 weeks of follow-up. Mortality is assessed in hospital by daily physician review and, post discharge, through study visits and by telephone where possible for children who are lost to follow-up. Morbidity during hospitalisation is assessed through daily clinical assessments and available hospital laboratory tests. Morbidity after discharge is assessed, first, using daily morbidity diaries, in which caregivers record episodes of illness (lethargy interfering with feeding; respiratory distress; diarrhoea; oedema and fever); second, from caregiver recall and review of handheld medical records at each follow-up visit; and, third, from data collected during hospitalisation for children who are readmitted during the follow-up period. Time-to-recovery from malnutrition will be evaluated during hospitalisation; relapse of malnutrition during follow-up will be categorised as moderate acute malnutrition, uncomplicated SAM and complicated SAM, according to WHO definitions. Nutritional outcomes will be expressed both as continuous variables (attained Z-score and change in Z-score between visits), and as categorical variables (moderate wasting, WHZ<–2; severe wasting, WHZ<–3; stunting, HAZ<–2; severe stunting, HAZ<–3; underweight, WAZ <–2; and microcephaly, head circumference-for-age <–2).

Risk factors will be evaluated at baseline, hospital discharge and over the period of follow-up for associations with clinical and nutritional outcomes. In addition to baseline clinical and demographic factors, the following laboratory parameters will be evaluated: haemoglobin, serum albumin, C reactive protein (CRP), CD4 count and HIV viral load (for HIV-positive children). Haemoglobin, CD4 and HIV-viral load will be measured in real time and the results reviewed during follow-up clinics.

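### Immunology substudy: post-discharge morbidity is recorded as repeated, dated episodes over unequal follow-up, but the only model named for it is binary logistic regression

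*Protocol article*

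**What the plan says.** In the protocol article, the Immunology substudy part of the Analysis section states: "Binary logistic regression will determine whether innate immune profiles at discharge are associated with morbidity or mortality during follow-up". No count, rate, duration or recurrent-event model is named for this question.

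The morbidity data are richer than a yes/no. Under Study outcomes and risk factors, post-discharge illness is captured "using daily morbidity diaries, in which caregivers record episodes of illness", supplemented by recall and handheld records at each visit and by data from readmissions. Table 2 schedules the diary "Daily during follow-up period by caregivers", and Study design says "All participants with SAM are followed for 48 weeks post discharge".

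Elsewhere the article uses fuller models. The in-hospital part of the same substudy is analysed "using logistic models for binary outcomes and linear models for duration". The main cohort's outcomes over 48 weeks, morbidity included, are analysed "using multivariable analysis (Cox models for time-to-event data, linear models for continuous outcomes").

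On size, Sample sizes, Immunology substudy says: "We will aim for 100 children with longitudinal analysis of innate immune cell function at discharge, 12, 24 and 48 weeks post discharge".

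**The concern.** Logistic regression accepts only a yes/no outcome and, as stated, has no term for time observed. Two kinds of information are lost.

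- **Frequency.** Children on the same side of the cut count alike, whether they had one episode or ten.
- **Observation time.** A child lost at week 4 without illness is coded the same as a child followed illness-free for the whole period. The article lists high loss to follow-up as a limitation, and its cohort sample-size section assumes 15% deaths and 15% losses. Table 2 also lets the final visit fall anywhere from week 44 to week 71 plus 6 days.

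This is the regression that bears most directly on the substudy's third hypothesis, that "nutritional rehabilitation only partly restores innate immune cell function, leading to an ongoing risk of bacterial infections post discharge". It will rest on about 100 children, so there is little power to spare. A moderate gradient in illness rate could be missed for want of a better-suited model, although the data for that model are already being collected.

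**Working it through.** **1. The plan's own figure.** The only power statement for this substudy concerns infectious mortality: n = 200, 15% events, two-sided alpha 0.05, 80% power, OR 1.7. The standard formula for a continuous covariate, taking the OR as per SD (the article does not state the unit), is

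n = (1.96 + 0.84)² / [p(1 − p)(ln OR)²].

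With p(1 − p) = 0.15 × 0.85 = 0.1275 and n = 200, ln OR = 2.80/√25.5 = 0.555, so OR = 1.74. This matches the printed 1.7 after rounding. At exactly 1.70 the power is 76.4%, and 219 children would be needed for 80%. No power figure is given for post-discharge morbidity.

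**2. The same formula at n = 100.** With 50% of children having the outcome, ln OR = 2.80/√25 = 0.560 and OR = 1.75. With 80%, ln OR = 2.80/√16 = 0.700 and OR is about 2.0. Only fairly steep gradients are detectable from a binary outcome.

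**3. Number of children.** The target is 100. Applying the cohort's 15% + 15% attrition gives 100 × 0.70 = 70, the same fraction as the article's 560 of 800. Seventy is pessimistic for a rate model, because children who leave early still contribute time.

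**4. Power by simulation.** *Assumptions, none in the documents:* immune profile standard normal; episode counts negative binomial with dispersion 0.5 or 1.0; rate ratio 1.3 or 1.5 per SD; complete follow-up; 500 runs per cell (standard error about 2 points); two-sided 5%. Compared are logistic any/none, logistic median split and a quasi-Poisson count model. Ranges run over the four combinations of dispersion and rate ratio.

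| n | Mean episodes per child | Power, any/none | Power, count | Loss, any/none (points) | Loss, median split (points) |
|---|---|---|---|---|---|
| 70 | 0.5 | 17–44% | 25–56% | 5–13 | 6–13 |
| 70 | 1 | 21–52% | 34–75% | 13–23 | 12–21 |
| 70 | 2 | 20–51% | 44–87% | 24–37 | 16–21 |
| 70 | 3 | 15–42% | 46–93% | 30–51 | 15–20 |
| 70 | 5 | 13–33% | 49–95% | 36–62 | 13–27 |
| 100 | 0.5 | 25–57% | 32–71% | 7–18 | 7–18 |
| 100 | 1 | 23–65% | 43–90% | 20–27 | 16–23 |
| 100 | 2 | 26–63% | 57–96% | 30–39 | 11–24 |
| 100 | 3 | 19–57% | 62–98% | 41–54 | 9–24 |
| 100 | 5 | 17–42% | 65–100% | 48–67 | 7–23 |

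**5. With unequal follow-up.** A second set used n = 70 to 100, 30% leaving early, dispersion 0.7 to 2.0, rate ratio 1.25 to 1.4, and log observed time as offset in the rate model. The any/none loss was about 10 to 55 points at 1 to 4 episodes per child and about 0 to 15 points at 0.5 or fewer. With no true effect, both methods rejected in about 3 to 8% of runs, so the gain is not bought with false positives.

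**6. How firm the edges are.** I re-ran the unequal-follow-up design over the wider grid (rate ratio 1.25 to 1.5, dispersion 0.5 to 2.0, 500 runs per cell, quasi-Poisson with offset). Most cells at 1 to 4 episodes lay within 10 to 55 points. The extremes were 6 (n = 70, mean 1, dispersion 2.0, rate ratio 1.25) and 63 (n = 100, mean 4, dispersion 0.5, rate ratio 1.4). The quoted range is therefore rounded at both ends.

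**The case against.** The strongest reply is that the article prints no cut. It speaks only of morbidity or mortality during follow-up, and a condensed article may leave the definition of the binary variable to the full protocol or analysis plan. The substudy is about bacterial infection, whereas the diary records non-specific signs. If morbidity here means readmission or severe infection, the outcome is uncommon and close to 0/1, and logistic regression costs little. This stands: at 0.5 events per child or fewer the loss is only about 0 to 18 points.

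It is also fair that the simulations generate counts from the family being fitted, with error-free diaries and exit unrelated to illness. Under-recording by caregivers and death-related exit would weaken the rate model too. With dispersion 2.0 and a rate ratio of 1.25, the rate model itself reached only 24 to 26% power at 1 to 2 episodes, so it does not rescue the test everywhere.

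A reader might infer that an any/none outcome barely separates these children because nearly all will fall ill. The documents give no episode rate. In simulations with 20% leaving early and dispersion 0.7, the share with any episode was 0.49, 0.67 and 0.81 at means of 1, 2 and 4. The first of these is close to the most informative binary split.

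A reader might also infer that a null result will be taken as proof of no relation. The Analysis section says the opposite: all analyses are exploratory, and p values are read as strength of evidence.

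What the reply does not remove is that the model type is fixed in the text. However morbidity is coded, a yes/no outcome without a time term cannot use episode frequency or unequal observation.

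**Conclusion.** The point holds in conditional form. For a recurrent outcome, the named model discards how often a child was ill and how long the child was watched, and no reason is given for using less here than in the in-hospital analysis or the main cohort.

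The size depends on a cut, an episode rate, a rate ratio and a dispersion that the article does not give. With an any/none cut and the assumptions above, the loss is about 10 to 55 points of power at 1 to 4 episodes per child and about 0 to 18 at 0.5 or fewer. With a median split it is about 7 to 27 points at 1 to 5 episodes.

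An unconditional statement that the plan loses tens of points of power, or throws away most of the information, goes beyond the documents. The latter holds only from about two episodes per child upward under an any/none cut. Nor does the point extend to logistic regression for mortality. Given the exploratory status, this is a worthwhile, inexpensive improvement and not an error that undermines a stated conclusion.

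**What to change.** In Analysis, Immunology substudy, replace the sentence on discharge profiles with wording to this effect: recurrent post-discharge morbidity will be analysed as the number of illness episodes, by negative binomial (or quasi-Poisson) regression on the discharge immune profile with log child-time observed as offset, or as recurrent events with a robust variance; logistic regression will be kept for mortality and for events that happen at most once.

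The cost is about one sentence, and the diary, visit and readmission data are already collected. Two small pieces of work follow: a rule for when a new episode starts in the diary, and a definition of time observed for each child (from discharge to death, loss or last completed diary). The rate model assumes that leaving follow-up is unrelated to illness, so the number of deaths and losses should be reported beside it.
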